### Outcome Measures

#### Primary outcomes

##### 1. ROM Active and Passive

All ROM tests are conducted using a manual, plastic, 2-group goniometer with 1-degree increments. The goniometer is centred on the knee joint. The distal reference marker is the peroneal malleolus and the proximal reference point is the greater trochanter in the hip [17]. To make sure that the goniometer is centred on the knee axis point, the patient is asked to bend and extend the knee a couple of times. This axis point should not change in the flexion and extension movement. For the measurement of the active flexion ROM, the patient is sitting in a chair and is asked to bend the knee as much as possible. For passive flexion ROM, the assistant helps the patient to bend until the patient indicates that it is the maximum point.

For the active extension ROM, the patient is lying in the supine position on a bed and is asked to stretch the knee as far as possible. For passive extension ROM, the assistant helps the patient to stretch until the patient says it is the maximum point.

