**Methods/design::**

The study is a randomized, open-label with blinded outcome assessor, parallel assignment clinical trial with a sample size of 52 patients that is conducted according to the SPIRIT recommendations. After the TKA intervention, the patients are randomly allocated to the control group or the experimental group with a 1:1 ratio. Both groups follow a Fast Track recovery protocol which includes discharge after 2–3 days from surgery, a daily plan of 5 exercises for autonomous rehabilitation and domiciliary visits by a physiotherapist starting approximately 2 weeks after surgery. The experimental group uses the sensor-based telerehabilitation system ReHub to perform the exercises. The primary outcome measure is the range of motion of the knee. Secondary outcomes include physical performance, quality of life, pain intensity, muscle strength, treatment adherence and satisfaction with the ReHub system. The outcomes assessment is performed at hospital discharge (baseline), at stitch removal (2 weeks after baseline) and 2 weeks after stitch removal (4 weeks after baseline).

The study conforms to the guidelines of the Declaration of Helsinki and was approved by the hospital’s ethics committee.

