## Methods

### Study design and randomization

The study is a prospective, randomized, controlled, parallel-group, open-label with blinded assessor trial that is conducted according to the SPIRIT recommendations [16]. Following informed consent, patients are randomized (with a 1:1 allocation ratio) to a control group or an experimental group. Computer-generated randomization lists are used (using the website www.randomization.com) to sequentially distribute the patients into one of the two groups. The primary outcome measure is knee Range of Motion (ROM).

The study conforms to the guidelines of the Declaration of Helsinki, was approved by the hospital’s ethics committee (“Comité Ético de Investigación Clínica del HCB”, reg. HCB/2019/0571), and registered at the ClinicalTrials.gov website (identifier NCT04155957).

A flow diagram of the study design is shown in ***Figure 1***.

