### Sample size estimation and statistical analysis

Sample size estimation was performed considering active knee flexion Range of Motion as the outcome measure. Considering a power of 80%, a two-sided significance level of 0.05 and a dropout rate of 10%, to detect a 10° difference between the two groups, a sample size of 52 patients will be needed. A standard deviation of 12° was determined by previous clinical trials [25,26].

The statistical analysis over the results will be performed by a blinded expert. Within and between-group comparisons will be performed by Two-sample t-test or one-way and two-way ANOVA analysis.

Data will be expressed as mean ± standard deviation (normally distributed data) or median and interquartile range (non-normally distributed data). The threshold for statistical significance will be set to P = 0.05. Missing data will be treated with the Last Observation Carried Forward method.

All statistical tests will be performed with Matlab (The MathWorks, Inc., Natick, Massachusetts, United States) software package.

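### The primary outcome is four ROM measures at two follow-up visits with none singled out, while the sample size covers one test of active flexion

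*Protocol article*

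**What the plan says.** - **Study design and randomization**: "The primary outcome measure is knee Range of Motion (ROM"), with no movement, mode or visit given.
- **Outcome Measures, Primary outcomes** (a plural heading): the single entry is "ROM Active and Passive". The text below it describes how four readings are taken: active flexion, passive flexion, active extension and passive extension.
- **Interventions**: the list of outcome measures has active and passive ROM as separate items, each covering flexion and extension. Table 2 schedules knee ROM at all three visits.
- **Abstract, Methods/design**: the assessments after baseline are "at stitch removal (2 weeks after baseline) and 2 weeks after stitch removal (4 weeks after baseline").
- **Sample size estimation and statistical analysis**: "Sample size estimation was performed considering active knee flexion Range of Motion as the outcome measure". The difference is 10°, the SD 12° and the power 80%, with "a two-sided significance level of 0.05". No visit is given. The same section sets one criterion for all tests, "The threshold for statistical significance will be set to P = 0.05", and allows a t-test or a one-way or two-way ANOVA.

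The article does not rank the four readings, choose a visit, or say what result would count as success.

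**The concern.** The sample size calculation treats the trial as having one primary test. The outcome section declares several. Both statements are in the article, and they do not describe the same analysis.

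Two things follow. If a significant result on any listed ROM measure at either visit can be reported as success on the primary outcome, the 5% error rate does not hold for that claim. If the measures are instead corrected for multiplicity later by splitting alpha, the 80% power does not hold for the 10° difference.

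The open visit adds to this. During the last two weeks both arms receive external physiotherapist sessions at home, 2 to 3 days a week and up to 10 in all. The 2-week comparison therefore largely sets ReHub against unsupervised exercise. The 4-week comparison sets ReHub plus those sessions against unsupervised exercise plus those sessions. Both are valid randomised comparisons, but they answer different questions, and nothing in the article prevents the choice between them being made once the results are known.

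**Working it through.** **Inputs from the article.** Difference 10°, SD 12°, two-sided alpha 0.05, power 80%, dropout 10%, allocation 1:1 (sample size and study design sections). Four ROM readings (primary outcomes and outcome list). Two visits after baseline (abstract and Table 2).

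**Step 1: reproduce the stated sample size.**

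n per arm = 2 × (1.960 + 0.842)² × (12/10)² = 2 × 7.85 × 1.44 = 22.6, rounded up to 23.

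Total 46; 46 / 0.90 = 51.1, rounded up to 52.

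This is the stated figure, so the arithmetic is correct for one test of active flexion. (The t-based version gives 24 per arm, or 54 after dropout, which is close.)

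**Step 2: count the eligible tests.** 4 readings × 2 visits = 8 between-group comparisons. A two-way ANOVA pooling visits would leave 4.

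**Step 3: chance of at least one false positive at 0.05 per test.** Under independence this is 1 − 0.95^k:

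- k = 8: 1 − 0.95^8 = 0.337
- k = 4: 1 − 0.95^4 = 0.185
- k = 2 (active flexion at both visits): 1 − 0.95² = 0.098

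The readings are correlated, and the article gives no correlations. The values below are therefore assumptions. They come from simulating equally correlated normal test statistics (400,000 draws).

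| Assumed correlation | 8 tests | 4 tests | 2 tests |
|---|---|---|---|
| 0 | 34% | 19% | 10% |
| 0.3 | 30% | 17% | 9% |
| 0.5 | 25% | 16% | 9% |
| 0.7 | 19% | 13% | 8% |
| 0.8 | 16% | 11% | 8% |
| 0.9 | 12% | 9% | 7% |

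A structured correlation may be closer to reality. With 0.3 between flexion and extension, 0.8 between active and passive, and 0.6 between visits, the eight-test figure is 24%. Three other structures of this kind, with values of 0.2 to 0.5, 0.8 to 0.9 and 0.5 to 0.8 respectively, gave 19% to 26%.

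**Step 4: power for 10° if alpha is split.** Evaluable patients per arm: 52 × 0.90 / 2 = 23.4. Standardised difference: 10/12 = 0.83.

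| Alpha per test | t-test, 23.4 per arm | z formula, 23 per arm |
|---|---|---|
| 0.05 | 80% | 81% |
| 0.05/4 = 0.0125 | 60% | 63% |
| 0.05/8 = 0.00625 | 50% | 54% |

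Restoring 80% power under Bonferroni, by the same z formula, would need 33 per arm for four tests (66 / 0.90, or 74 recruited) or 37 per arm for eight (74 / 0.90, or 83 recruited).

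**The case against.** The strongest reply is that the intended primary is clear enough. The abstract and the design section speak of one outcome measure, and the trial is sized on active flexion, for which 52 patients is right. This is also a journal article, and hierarchy, multiplicity handling and the exact contrast are usually set out in a full protocol or analysis plan. A blinded analyst and blinded assessors limit selective reporting.

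Active flexion is indeed the natural guess, but the section that defines the primary outcome says otherwise, and the guess still leaves two visits open. The point does not depend on detail missing from an unseen plan. A plan that selected one reading would depart from the outcome section as published, and one that split alpha would depart from the published power. Blinding the analyst to arm does not hide which of eight two-sided tests falls below 0.05.

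Four further qualifications stand:

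- Eight is an upper count; the ANOVA option could make it four.
- The 34% figure needs independence, which is implausible for repeated readings on one knee. The lower figures are the more realistic ones, and they rest on assumed correlations.
- The loss of power applies to splitting alpha. A fixed order beginning with active flexion at one visit would keep the full 0.05 for that test, but the article states no such order.
- No success rule is stated. If every reading had to succeed, alpha would be protected, but the joint power would then be something the sample size paragraph does not address.

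**Conclusion.** The concern holds, and the primary outcome is wrong as written. Several readings at two visits are declared primary, and alpha and power are stated for one of them without a visit. If any single significant result may count, the error rate of the primary claim is above 5% in every case examined: 34% at most for eight tests, 12% at an assumed correlation of 0.9, and 9% for four tests at that correlation. Even active flexion alone, tested at both visits, gives 7% to 10%. The true value within these ranges cannot be fixed from the article. The total of 52 is not in dispute; it is correct for a single active-flexion test. Because the defect bears on the trial's main efficacy claim, it must be corrected.

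**What to change.** Name one primary endpoint: active knee flexion ROM at the final (4-week) visit, compared between arms at two-sided 0.05. This matches the variable used for the sample size and the end of the 4-week programme. List passive flexion, active extension, passive extension and all 2-week ROM comparisons as secondary, and attach the 4-week visit to the sample size statement.

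Make the change before any unblinded analysis, and date it. The Trial Status section reports recruitment as ongoing, so at the time of the article this was still possible.

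The cost is wording in the protocol, and in the registry entry where that differs (the entry was not available for this review). Sample size and alpha do not change. The only loss is the option to claim primary success on another ROM measure or at the earlier visit.

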#### Secondary outcomes

##### 1. Timed Up-and-Go

The Timed Up-and-Go (TUG) test measures the time required for standing up from a chair, walking straight for 3 meters, turning, walking back to the chair, and sitting down [18]. The nurse is in charge of indicating when to start the test.

##### 2. Muscle strength

The maximal isometric voluntary contraction of the operated leg is assessed using a handheld dynamometer (Lafayette Manual Muscle Tester) [19]. The muscle strength test of the knee extension is performed for the quadriceps and then the knee flexion test is performed for the hamstrings. Knee extension is assessed with the participants in sitting position with their feet on the floor and with the hip at 90° of flexion.

##### 3. VAS

To assess the pain level, the patient is asked to rate the pain he/she feels on a Visual Analog Scale that ranges from 0 to 10, with 0 being «no pain» and 10 being the “worst pain imaginable” [20].

##### 4. WOMAC – EuroQoL-5D-5L

WOMAC (Western Ontario and McMaster Universities Osteoarthritis Index) [21,22] and EuroQoL-5D-5L [23] are standard questionnaires which are self-administered by the patients and will be compared with the baseline later in the analysis to explore the improvements in the quality of life of the patients in both groups of the study.

##### 5. Adherence

The adherence to the home exercise program is measured by obtaining the percentage of exercises done from the ReHub database for the experimental group and from the exercise diary filled by control patients in the control group.

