### Interventions

Patients are normally discharged 48 hours after the operation with an updated physiotherapy schedule and a leaflet containing the exercises and patterns to follow. The physiotherapist makes sure that the patients (from both groups) have understood them and will perform them correctly.

The rehabilitation program duration per patient is 4 weeks (30 days) after hospital discharge. Three visits take place, one at discharge (baseline), another after 2 weeks and the final visit after 4 weeks (***Table 2***).

**Table 2 T2:** Timepoint chart.

	RECRUITMENT	BASELINE VISIT	INTERVENTION (2 WEEKS)	FOLLOW-UP VISIT	INTERVENTION (2 WEEKS)	FINAL VISIT

**TIMEPOINT**	**-t_o_**	**t_0_**		**t_1_**		**t_2_**

Screening & Eligibility	X					

Informed consent procedure	X					

Treatment randomization	X					

ReHub training (Experimental Arm only)			X			

Timed Up-and-Go		X		X		X

Knee ROM		X		X		X

Muscle strength		X		X		X

Pain level (VAS)		X		X		X

WOMAC		X		X		X

EuroQol-5D-5L		X		X		X

Patient diary data collection (Control Arm only)						X

System Usability Scale (Experimental Arm only)						X

Adherence						X

Adverse events				X		X

The following outcome measures are collected for the patients at the visits:

Active Knee ROM (°) with a goniometer, both flexion and extensionPassive Knee ROM (°) with a goniometer, both flexion and extensionTimed Get-Up-and-Go test (s)Quadriceps muscle strength with a dynamometer (kg)Hamstring muscle strength with a dynamometer (kg)Pain Level with a Visual Analog Scale (VAS)Western Ontario and McMaster Universities Osteoarthritis Index (WOMAC)EuroQol-5D-5L scoreAdherence to exercise program (only collected in last visit)System Usability Scale (only collected in last visit for experimental patients)

Both groups shall perform at home the prescribed exercises. The control group will follow the common home rehabilitation recommendations and exercise autonomously while the experimental group patients will use ReHub to perform their exercises; for both groups the exercise pattern will be the same.

In addition, and as part of the usual hospital protocol, during the last two weeks, the participants of both groups will receive a visit from a physiotherapist from an external company, 2–3 days per week, up to 10 sessions. The details of the intervention for each group are as follows:

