Experimental Group:A site team physiotherapist will make three home visits during the 4 weeks. In the first visit (the day after discharge), the patient receives a ReHub bag including a tablet with ReHub installed and the Exercise Kit. The site team physiotherapist explains how ReHub works and how to perform exercises. The second visit (second day after discharge) is a follow-up visit to ensure the correct use of ReHub so the patient can perform his/her exercises properly. An optional third visit can be planned for the following day at this stage if the patient has difficulties using the platform. The patient follows the exercise program with ReHub, and a site team physiotherapist monitors the patient’s progress daily through the platform.12–17 days after surgery, the patient attends the hospital for stitch removal and the second visit takes place. If required, in this visit the therapy is reprogrammed. The day after the second visit, a site team physiotherapist makes the last home visit to ensure no problems have arisen during the last 2 weeks.Around 30 days after the surgery, patients attend the hospital for the final control. In addition to the aforementioned outcome measures, patient satisfaction with ReHub is measured by the administration of the System Usability Scale as well.Control Group:The 3 main visits are the same as the experimental group and the same outcomes are measured. The control group does not receive home visits from the site team physiotherapists. Patients are asked to fill out a diary to indicate which exercises they performed and the corresponding dates. At the final visit at the hospital, in addition to collecting the aforementioned outcome measures, the patients’ exercise diary will be collected.

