### ReHub telerehabilitation system

ReHub is a digital platform for physical rehabilitation that offers personalized design and monitoring of therapeutic exercise programs to recover the functional capacity of the musculoskeletal system.

The solution is composed of two main pillars; a cloud platform and an exercise kit that includes an inertial motion sensor. The cloud platform establishes communication between the patient and the healthcare professionals in charge of their rehabilitation. It allows physical therapists to create a rehabilitation program specifically tailored to each patient’s condition. A dashboard allows the professional to follow the progress of the patient, see the results of the exercises performed and adapt the program remotely.

Patients use the cloud platform to perform the exercises in their rehabilitation program with the help of DyCare’s proprietary wearable sensor that captures 3D motion data. The sensor is integrated into different exercise tools that help the patient performing different kinds of exercises make up the rest of the kit, though only a body strap is used in this trial as the exercises in the rehabilitation program designed by the hospital do not require additional tools. The sensor records biomechanical parameters such as range of motion and speed in real-time when used on the indicated body part while exercising. When patients do their prescribed exercises at home, intelligent algorithms deliver real-time biofeedback through a User Interface and a Virtual Coach. The results can be viewed by the physiotherapist to follow the progress of the patient, adapt the program remotely if needed or chat with them with the online messaging module through the platform.

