## Discussion

This study aims to assess the effectiveness of a home-based telerehabilitation program for the improvement of physical function and clinical outcome following TKA.

In addition, patient satisfaction with the telerehabilitation solution (ReHub) is evaluated to explore whether it increases the adherence to the treatment among other improvements. Another important point of the study will be the evaluation of the costs of the rehabilitation process with the ReHub program compared to conventional rehabilitation and as a result, the economic effects it can have, particularly for the public health system.

The randomized controlled design, blinding of the individual performing the outcome assessments, and use of valid tools for the assessment of physical performance and muscle strength (TUG score and dynamometer-based measurements of muscle strength under isometric conditions, respectively) are notable strengths of the study.

However, the short duration of the intervention (4 weeks) and the lack of a long-term follow-up that could help determine with more precision whether telerehabilitation could have lasting benefits could be a limitation to our study. Also, the fact that the adherence of control patients to their exercise program is self-reported in an exercise diary, could affect the evaluation of this parameter.

Notwithstanding these limitations, demonstrating the effectiveness of a home-based telerehabilitation program for physical function and/or muscle strength improvement following TKA could have relevant implications for the post-surgical rehabilitation process. In fact, telerehabilitation solutions could facilitate access and adherence to health interventions, reduce health care costs (associated with supervision, facility provision, and transport of patients), and also contribute to social distancing when it becomes necessary as an infection control action. In addition, the results of the study could support the systematic incorporation of solutions like ReHub in post-surgical rehabilitation protocols, that should be tailored to the individual and collective needs.

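### Adherence comes from a device log in one arm and a self-completed diary in the other, so a between-arm difference mixes any ReHub effect with the difference between instruments

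*Protocol article*

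**What the plan says.** All references are to the protocol article.

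- **Status.** The abstract names adherence among the secondary outcomes: "Secondary outcomes include physical performance, quality of life, pain intensity, muscle strength, treatment adherence".
- **Definition.** Under Secondary outcomes, 5. Adherence, it is "measured by obtaining the percentage of exercises done", obtained "from the ReHub database for the experimental group and from the exercise diary filled by control patients".
- **Diary.** Table 2 (Interventions) has a row "Patient diary data collection (Control Arm only"), marked at the final visit. The control-group description in the same section reads: "Patients are asked to fill out a diary to indicate which exercises they performed and the corresponding dates".
- **Log.** The section on the ReHub system states: "The sensor records biomechanical parameters such as range of motion and speed in real-time when used on the indicated body part while exercising".
- **Analysis.** The statistical section gives one general rule: "Within and between-group comparisons will be performed by Two-sample t-test or one-way and two-way ANOVA analysis". It does not exempt adherence.
- **Use.** The Discussion says the study will explore whether ReHub raises adherence. It also lists as a limitation that "the adherence of control patients to their exercise program is self-reported in an exercise diary, could affect the evaluation of this parameter".

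**The concern.** A between-arm comparison estimates a treatment effect only if both arms are measured in the same way, or if the difference in measurement is known. Here the instrument changes with the arm. A diary records what the patient chooses to write down. The log records what was done with the system in use. The two can err for different reasons and by different amounts.

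The Background gives reliance on what patients and families report as the reason why adherence to the home programme is currently unknown. The trial then keeps that source in one arm only.

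What is at stake is any statement that ReHub does or does not improve adherence. Data collection fixes this problem, so a later analysis plan could restrict the comparison but could not repair it.

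**Working it through.** **1. The plan's own figure.** The documents give no adherence figure (level, SD or target difference). The only sample size is for active knee flexion: difference 10°, SD 12°, two-sided 0.05, power 80%, dropout 10%.

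n per arm = 2 × (1.960 + 0.842)² × 12² / 10² = 22.6, rounded up to 23, so 46 in total. Then 46 / 0.9 = 51.1, rounded up to 52. The stated 52 is reproduced, and the adherence point does not touch it.

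**2. What the adherence contrast estimates.** Let A_E and A_C be true mean adherence in the experimental and control arms, and e_log and e_diary the mean errors of the two instruments. Then:

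observed difference = (A_E − A_C) + (e_log − e_diary)

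The trial observes one mean per arm, and each arm has its own instrument. Nobody is measured by both, so the second bracket cannot be estimated from the trial's data.

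**3. Direction.** The error values here are assumed; the documents give none. A negative bias acts against ReHub.

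| Assumed errors | e_log − e_diary |
|---|---|
| Diary over-filled by 10 points, log misses 5 | −5 − 10 = −15 |
| Diary over-filled by 20 points, log misses 5 | −5 − 20 = −25 |
| Diary incomplete by 10 points, log misses 5 | −5 + 10 = +5 |

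The sign depends on which errors occur, and the documents do not settle that.

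**4. Size, as an illustration.** Assume 23 analysed patients per arm (from step 1), equal true adherence, a net instrument shift of b points and an adherence SD of 15 to 30 points. With SE = SD × √(2/23), the chance of a significant difference at two-sided 0.05 is Φ(b/SE − 1.96) + Φ(−b/SE − 1.96).

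| SD | b = 5 | b = 10 | b = 15 | b = 20 |
|---|---|---|---|---|
| 15 | 20.4% | 61.8% | 92.4% | 99.5% |
| 20 | 13.6% | 39.6% | 72.0% | 92.4% |
| 25 | 10.4% | 27.4% | 53.0% | 77.4% |
| 30 | 8.7% | 20.4% | 39.6% | 61.8% |

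For example, with SD 15 and b = 10, SE = 15 × 0.295 = 4.42 and b/SE = 2.26. Then Φ(0.30) = 0.618, and the second term is negligible. The nominal rate is 5%.

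The reverse case assumes a true ReHub advantage of 15 points and diaries over-filled by 10, which leaves 15 − 10 = 5 points visible. Power, Φ(d/SE − 1.96), falls from 72.0% to 13.3% at SD 20, from 53.0% to 10.0% at SD 25, and from 39.6% to 8.2% at SD 30.

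**The case against.** The strongest reply has four parts.

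**It is already disclosed.** The Discussion does name control self-report as a limitation. That stands, but it covers the diary alone. It does not mention that the arms are measured differently, and it does not limit how the comparison is used.

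**The choice is practical and the outcome is secondary.** Giving controls the sensor system would hand them part of the intervention. The statistical section's rule is general and does not name adherence, and the Discussion speaks only of exploring it. All of this is fair, and it limits the weight of the point. It does not make the two percentages comparable.

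**The bias may be harmless to a positive finding.** A reader might infer that over-filled diaries and missed log entries both work against ReHub, so that an observed advantage is conservative. A reader might equally infer a known bias of 15 to 25 points. The documents support neither. They give no reporting error, and an incomplete diary would act in ReHub's favour.

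**Some possible mechanisms are not documented.** This is correct. Software failures appear only as examples of adverse events, and nothing says that log records are lost or that exercises are done without the tablet. A reader might also infer different denominators, because the ReHub programme can be reprogrammed or adapted remotely. However, the Interventions section says the exercise pattern is the same in both groups, and nothing says the percentage is taken against anything other than the prescribed plan. These remain possibilities, and the point does not depend on them.

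**Conclusion.** The concern holds for the between-arm contrast. As planned, neither a difference in adherence nor its absence can be attributed to ReHub, because instrument and arm coincide and no patient links the two. The size and net direction of the bias are unknown. The false-positive and power figures show only how sensitive the comparison is under assumed SDs and shifts; they are not estimates for this trial.

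A reader might conclude that the adherence data cannot be interpreted at all. That goes too far: each arm's adherence can be described from its own source, with the source named. The primary outcome and the sample size of 52 are unaffected. The change is advisable because the remedy is cheap and the trial intends to say something about adherence.

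**What to change.** **Minimum.** State that adherence is reported descriptively by arm, each from its own source, with no between-arm significance test and no claim that ReHub increases adherence. Extend the limitation in the Discussion to the mismatch between arms. This costs only a change of wording.

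**Preferably also.** Trial Status reports that recruitment is ongoing, so give the existing diary to experimental patients still to be recruited. Compare diary percentages, against the same prescribed plan, as a supportive analysis in those later patients. Keep the ReHub log as a within-arm measure and as a check of agreement between diary and log in the experimental arm. Do not apply that agreement to controls, whose reporting is not monitored.

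**Costs of the second step.**
- Experimental patients carry a small daily burden.
- A self-monitoring prompt is added to the experimental arm part-way through the trial.
- The like-for-like comparison covers later patients only.
- Some reporting bias remains, because patients are unblinded and ReHub users know that a physiotherapist follows them. A shared diary removes the difference in instrument but does not guarantee equal error.
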